##### Internet-delivered cognitive behavioral therapy for tinnitus (ICBT)

The ICBT intervention for the experimental group will start after group allocation. The ICBT is based on a self-help program created by Andersson and colleagues and is designed to address the physical, emotional, and problematic effects of tinnitus for habituation [35]. The program includes key audiological principles and has been modified previously to an interactive e-learning format for better engagement [10]. The 16 recommended modules and 5 optional modules can be tailored to individual needs and are released weekly over an 8-week period. Participants are encouraged to engage with the modules and practice the suggested techniques daily. The program is comprehensive, offering a range of CBT techniques, and can be accessed online, downloaded, or printed. It includes information, videos, quizzes, diagrams, worksheets, and solutions for common problems. Participants can also use a secure messaging system to ask questions and receive feedback from their assigned program therapists.

##### Internet-delivered mindfulness-based tinnitus stress reduction.

The i-MBTSR course consists of 8 online lessons held weekly, which include videos, audio recordings, and written content covering tinnitus education, mindfulness, gentle yoga, and guided meditations [25]. Participants are required to do 30 min of daily meditation and attend a daylong practice session between the 6th and 7th week to enhance their mindfulness skills. The course aims to provide in-depth tinnitus education, reduce tinnitus-related anxiety, and teach meditation skills to help participants view tinnitus as a normal part of their sensory experience, reducing its bothersome effects. Just like the ICBT participants, individuals assigned to iMBTSR group will also have the ability to use the same secure messaging system to ask questions and receive feedback from their assigned program therapists.

#### Criteria for discontinuing or modifying allocated interventions {11b}

Participants will be instructed to notify the research staff in the event of a decline in their condition. Within 24 h, a trained clinical psychologist will conduct a thorough clinical assessment via telephonic interview. Based on the results of the evaluation, the participant may be referred for hospitalization or other necessary medical services.

#### Strategies to improve adherence to interventions {11c}

Adherence to the intervention protocols and reduction of attrition rates will be enhanced through strategies recommended by Dziura and co-authors [36]. These strategies involve data collection that does not necessitate in-person visits and frequent, guided communication throughout the trial. Participation is voluntary, and individuals have the right to withdraw without consequences. In exceptional circumstances, participants may be removed if they are unable to continue with the trial due to unforeseen reasons. The reasons for withdrawal will be documented.

#### Relevant concomitant care permitted or prohibited during the trial {11d}

Stable doses of ongoing psychopharmacological medications are permitted, but other psychological interventions are not allowed to start during the trial. If they are started after the intervention had ended, it will not result in disqualification from participating in follow-ups. After all the follow-ups, participants will be asked about receiving any other interventions during the study period, and this information will be reported with the study results.

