## Methods: participants, interventions, and outcomes

### Study setting {9}

This study will be conducted completely remotely. All screening and outcome questionnaires will be completed online and intake, and post-treatment interviews will be done on the phone. The intervention is provided via a web-based platform and is mobile device friendly. All participants who speak Lithuanian regardless of their place of residence will be considered for participation in the trial as long as they are available for an interview over the phone. The participant flowchart is shown in Fig. 1.

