### Sample size {14}

In order to attain 80% power with a 5% alpha level, a three-means non-inferiority test (ANOVA) was performed, resulting in a required sample size of 42 participants in total. To account for potential dropouts, the number of participants was increased by 25%, resulting in approximately 18 participants per study arm. This dropout rate is common for therapist-guided internet-based interventions. The primary end point used for the non-inferiority test was the THI score at 8 weeks, and the equivalence margin was determined to be 7 points, based on the mean minimally clinically important difference (MCID) found in a prior study [47].

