### Data collection and management

#### Plans for assessment and collection of outcomes {18a}

Data will be collected at pre-randomization, termination, and 3- and 12-month follow-ups. All questionnaires will be self-report and administered online. To ensure that collected data is complete and accurate, the online questionnaires will be coded in a way that requires participants to fully answer the questions in order to submit the answers. For a full timeline of questionnaire dissemination, see Table 1.

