#### Plans to promote participant retention and complete follow-up {18b}

All participants will be informed in the informed consent about follow-up assessments. If participants discontinue or deviate from intervention protocols, they will be contacted and study team members will first try to address any concerns participants might have that are altering their adherence to the intervention protocols. In case these concerns cannot be resolved, participants will then be asked to fill in follow-up self-assessment questionnaires online.

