### Methods in analysis to handle protocol non-adherence and any statistical methods to handle missing data {20c}

The results will be calculated based on the per-protocol approach and will also be compared with those obtained using the intention-to-treat approach. To perform the intention-to-treat analysis, a missing value analysis will be carried out. If necessary, missing data will be filled in using multiple imputation techniques.

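### The only question about other care that the protocol describes comes after the 12-month follow-up, too late and too incomplete for the week-8 per-protocol analysis

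*Protocol article*

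**What the plan says.** Concomitant care is covered in the Protocol article, section {11d}. Stable psychotropic medication is allowed, and starting another psychological intervention during the trial is not. Starts after the treatment period are then tolerated: "If they are started after the intervention had ended, it will not result in disqualification from participating in follow-ups". The section names one occasion for finding out: "After all the follow-ups, participants will be asked about receiving any other interventions during the study period". It adds that the answers will be reported with the results.

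Other sections bear on the point:

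- **Outcome schedule {18a}:** "Data will be collected at pre-randomization, termination, and 3- and 12-month follow-ups". The last planned assessment is thus 12 months after treatment.
- **Sample size {14}:** the primary endpoint for the non-inferiority test is the THI at 8 weeks.
- **Non-adherence and missing data {20c}:** "The results will be calculated based on the per-protocol approach and will also be compared with those obtained using the intention-to-treat approach".
- **Eligibility {10}:** exclusion criterion (3) is taking part in other tinnitus interventions while the study runs.
- **Adherence {11c}:** in exceptional circumstances "participants may be removed if they are unable to continue with the trial due to unforeseen reasons". Other care is not named there.
- **Retention {18b}:** people who stop or deviate from the intervention are contacted, and if the problem cannot be resolved, "participants will then be asked to fill in follow-up self-assessment questionnaires online".

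**The concern.** A prohibition that feeds a per-protocol analysis needs a record of who broke it, made close to the time it applies. Here the prohibition matters most in weeks 1 to 8, the per-protocol analysis of the primary endpoint concerns week 8, and the described question is put about a year later, to those who are still taking part.

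Two things are at stake. First, any per-protocol classification that uses other care would rest on long recall and would be blank for people lost between week 8 and month 12, even where their week-8 THI is in hand. If week-8 results are analysed before the last follow-up, the answers would not yet exist at all. Second, the report on other care that section {11d} promises would describe only those who reached the end.

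A secondary matter is what happens to a randomised participant who starts other care during the 8 weeks. Sections {10}, {11d} and {18b} can be read in different directions, and the intention-to-treat comparison needs that person's outcomes.

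**Working it through.** The plan gives no figure for this point, so the check is one of timing and text.

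**Inputs.** Treatment lasts 8 weeks, with the primary THI at week 8 (sections {11a}, {14}). Follow-ups are at 3 and 12 months after treatment ({18a}). The question on other care comes after all follow-ups ({11d}). I take 12 months as 52 weeks.

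**Recall under the plan, at the earliest possible time of asking (month 12).**
- Care started at the beginning of week 1: 8 + 52 = 60 weeks earlier.
- Care started at the end of week 8: 0 + 52 = 52 weeks earlier.
- Care started between week 8 and month 3: 12 − 3 = 9 months to 12 months earlier.

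**Recall with items at week 8 and month 3.**
- Care started in weeks 1 to 8: at most 8 weeks.
- Care started between week 8 and month 3: at most 3 months.

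**Is there an earlier occasion?** I looked for any other contact stated to ask about other care.
- Section {9} says that "intake, and post-treatment interviews will be done on the phone", but gives no content for the post-treatment interview.
- Section {11c} promises frequent communication and documented reasons for withdrawal. Neither is said to cover other care.
- Section {21a} describes weekly contact, for adverse events.
- Table 1 lists no item on other care. This is weak evidence, since the table also omits the final question and the post-treatment interview.

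No earlier question is described.

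**Who is not asked?** By this route, everyone lost before month 12. Their number is unknown. Purely as an illustration, section {14} says "the number of participants was increased by 25%, resulting in approximately 18 participants per study arm". The base is 42/3 = 14 per arm, and 42 × 1.25 = 52.5, or 17.5 per arm, rounded to 18. The allowance is 18 − 14 = 4 per arm, and 4/18 = 22%. If losses by month 12 were 2 to 6 per arm, 2/18 = 11% to 6/18 = 33% would go unasked. That allowance was set for a week-8 endpoint, so applying it to month 12 is my assumption, and the argument does not depend on it.

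**Follow-up status after an early start, side by side.**
- {10}, criterion (3): if read as applying after randomisation, it points to removal.
- {11d}: protects those who start after treatment and is silent on those who start during it.
- {11c}: the removal provision does not mention other care.
- {18b}: points to continued follow-up for those who deviate, without naming other care.
- {20c}: the planned intention-to-treat comparison needs the data.

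The balance favours retention, but no sentence says so for this case.

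**The case against.** The strongest reply is that this rests on silence. Section {11d} does not say that the final question is the only one; the post-treatment call, therapist messages and weekly contacts could all bring other care to light. The only use the article gives for the answers is reporting, and the definition of the per-protocol set may sit in an analysis plan that is not shown. Nothing in the documents shows that people forget having started a psychological treatment a year ago.

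Part of this stands. Other care might be learned by another route, and no effect on a result can be demonstrated. What remains is that the article fixes the timing of the one question it describes, and assigns the task to no earlier contact. An analysis plan written later can define a per-protocol set, but cannot recover answers that were never collected.

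A reader might also infer from the sentence protecting later starters that anyone who starts other care during the 8 weeks is disqualified, and that outcome data are thereby lost. The documents do not support that. The rule is nowhere stated, and the retention section and the intention-to-treat comparison point the other way. Nor would such a rule reach the primary endpoint as worded: the article uses follow-ups for the 3- and 12-month assessments, so the week-8 THI would not be affected.

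**Conclusion.** The point holds as a minor one about data collection. The protocol prohibits starting other psychological care, but describes asking about it only after month 12, some 52 to 60 weeks after any start in weeks 1 to 8, and by that route only of those who remain. That is too late and too incomplete a basis for the week-8 per-protocol classification, on the assumptions that other care enters that classification and that no undescribed contact records it earlier.

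The size and direction of any bias are unknown, because the share who will start other care is not given. The follow-up status of early starters is a matter for clarification, not a demonstrated contradiction or a loss of data.

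**What to change.** 1. Add one item on other interventions received, with approximate start date, to the existing online questionnaires at week 8 and at 3 months, and keep the final question.
2. Add a clarifying sentence: exclusion criterion (3) applies at entry; randomised participants who start other care at any time remain in all outcome collection (week 8, 3 and 12 months) and in the intention-to-treat set; a start during the 8 weeks counts only as a per-protocol deviation.

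No change to which care is permitted is needed. The cost is one extra item at two time points and a sentence of text. Intention-to-treat results will include any effect of other care, which is a reason to keep the per-protocol comparison beside them.

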#### Provisions for post-trial care {30}

We expect that participants will not experience any harm as a result of participating in the trial. However, participants who will show deterioration in their condition will be directed to health services accordingly.

### Outcomes {12}

We will assess the interventions’ effects on a few different areas of participants’ functioning. A primary outcome assessed will be the change in tinnitus impact on participants functioning in daily life. We will also assess as secondary outcomes changes in psychological difficulties associated with having tinnitus—depression, anxiety, and sleep difficulties. Participants’ cognitions about tinnitus and the frequency of state of mindful awareness will also be assessed as a secondary outcome in the study. Tinnitus, hearing problems, and hyperacusis will be assessed to screen the eligibility for the study and to assess any possible changes post-treatment. Finally, big five personality traits and other sociodemographic and health variables will be assessed to analyze the personal factors associated with interventions’ efficacy.

Measures included in the study and the time point for each measure will be the following.

#### Primary outcome measures

To assess the impact of tinnitus on daily life, the Tinnitus Handicap Inventory (THI) will be used [37]. Assessment with THI will take place at pre-treatment, post-treatment at week 8, and 3 and 12 months post-treatment follow-ups. Change in the score from baseline will be assessed. The THI is designed to assess the impact of tinnitus on daily life and measures tinnitus-related functional limitations and emotional and catastrophic reactions. It is also widely used in research studies to measure the change in the severity of a tinnitus handicap before and after an intervention and therefore was selected as the primary measure of the study. The THI questionnaire consists of 25 questions. Answers are scored as follows: “yes,” 4 points; “no,” 0 points; and “sometimes,” 2 points. The total score is obtained by summing the scores of all 25 questions. A higher score indicates a higher disability caused by tinnitus and a higher impact of tinnitus on a person’s daily life. A validated Lithuanian language version of THI will be used in the study [38].

Weekly monitoring of changes in tinnitus handicap severity will be done using the Tinnitus Handicap Inventory Screening version (THI-S) [39]. A screening version of THI has 10 items from the original THI and will let assess the changes throughout the duration of the program. Assessment with THI-S will be done at weeks 2, 4, and 6.

#### Secondary outcome measures

The severity of the depressive symptoms of participants will be measured with the Patient Health Questionnaire (PHQ-9) [40]. Assessment will be done pre-treatment, post-treatment (week 8), and at follow-ups (3 months and 12 months post-treatment). Change in the score from baseline will be calculated. PHQ-9 contains 9 questions answered on a 4-item Likert scale, where number 0 indicates “not at all” and 3 indicates “nearly every day.” Scores of all questions are summed for the total score, where a higher score indicates more severe symptoms.

The severity of participants’ anxiety will be assessed with Generalized Anxiety Disorder-7 (GAD-7) [41]. Assessment will take place pre-treatment, at week 8 and 3 months, and 12 months post-treatment, and change in score from baseline will be measured. The questionnaire contains 7 questions answered on a 4-item Likert scale, where number 0 indicates “not at all” and 3 indicates “nearly every day.” A higher score indicates more severe symptoms.

The insomnia symptomatology of participants will be assessed with Insomnia Severity Index (ISI) [42]. Time points for assessments will be pre-treatment, post-treatment at week 8, and 3 months and 12 months post-treatment. The questionnaire consists of 7 questions answered on a 5-item Likert scale from 0 (not at all) to 4 (very much), with a time interval of “within the last 2 weeks.” The scores for all 7 questions are summed, and the total score ranges from 0 to 28 points. A higher score indicates higher severity of insomnia.

To screen for hearing problems and sound tolerance problems (hyperacusis) that may interfere with participation in the intervention, Tinnitus and Hearing Survey (THS) will be used [43]. The measure will be used pre-treatment for screening and post-treatment at week 8, to assess any possible changes in score from baseline. The measure includes three subscales: tinnitus (4 items), hearing problems (4 items), and hyperacusis (1 item and 1 open question). Answers can range from 0 (not a problem) to 4 (very big problem). The total scores for tinnitus and hearing problems subscales can range from 0 to 16. Participants report their experiences in the last week to assess their current experience rather than their past history.

To assess the changes in the frequency of experiencing a state of mindful awareness, the Mindful Attention Awareness Scale (MAAS) will be used [44]. Assessment will be done pre-treatment, post-treatment (week 8), and at follow-ups (3 months and 12 months post-treatment); changes in scores from baseline will be assessed. The scale consists of 15 statements. Each statement is rated on a 6-point Likert scale (1 = almost always; 6 = almost never). Higher scores indicate a tendency to experience a more frequent state of mindful awareness, and a total score is either a mean or a sum of all answers.

To assess the changes in participants’ positive and negative cognitions related to tinnitus, the Tinnitus Cognitions Questionnaire (TCQ) will be used [45]. Assessment will be done pre-treatment, post-treatment (week 8), and at follow-ups (3 months and 12 months post-treatment), and changes in scores from baseline will be assessed. The questionnaire consists of 26 questions. Each statement is scored on a 5-point scale from 0 to 4 according to how frequently the cognition is thought (from 0 for “never” to 4 for “very often”). Negative items are scored from 0 to 4 and positive items from 4 to 0. The total score ranges from 0 to 104. A high score indicates a tendency to engage in negative cognitions in response to tinnitus rather than positive ones.

#### Other outcome measures

To assess the expressiveness of personality traits (extraversion, neuroticism, openness to experience, conscientiousness, and agreeableness), the Big Five Inventory (BFI-10) will be used in the pre-treatment assessment [46]. The questionnaire consists of 10 questions, two items per personality trait. Each statement is scored on a 5-point Likert scale (1 = strongly disagree and 5 = strongly agree). The higher the scores on the subscales, the more the personality trait is expressed.

Sociodemographic, tinnitus, and health-related questions will be assessed at pre-treatment. Questions to assess the eligibility for the study and to gather demographic and other important information will be used.

### Participant timeline {13}

Participant timeline is presented in Table 1.

**Table 1 Tab1:** Schedule of enrollment, interventions, and assessments

Assessment/activity	Online screening/baseline	Telephone interview	Post-randomization			Follow-up	
	* − t*1	*t*0	*t*1–*t*8 (weekly)	*t*1–*t*8 (biweekly)	*t*9 (post)	*f*1	*f*2
Informed consent	X						
Demographic data	X						
iCBT			X				
iMBTSR			X				
THI-S				X			
THI	X				X	X	X
PHQ-9	X				X	X	X
GAD-7	X				X	X	X
ISI	X				X	X	X
THS	X				X		
MAAS	X				X	X	X
TCQ	X				X	X	X
BFI-10	X						
Eligibility criteria		X					
Treatment expectancy		X					
Treatment engagement			X				

### Sample size {14}

In order to attain 80% power with a 5% alpha level, a three-means non-inferiority test (ANOVA) was performed, resulting in a required sample size of 42 participants in total. To account for potential dropouts, the number of participants was increased by 25%, resulting in approximately 18 participants per study arm. This dropout rate is common for therapist-guided internet-based interventions. The primary end point used for the non-inferiority test was the THI score at 8 weeks, and the equivalence margin was determined to be 7 points, based on the mean minimally clinically important difference (MCID) found in a prior study [47].

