### Trial design {8}

This study is three-armed parallel-group randomized controlled non-inferiority trial. Participants will be randomized to all groups equally.

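### The 25% dropout allowance is applied as a multiplier, so 18 per arm falls just short of the required 42 completers if 25% are in fact lost

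*Protocol article*

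**What the plan says.** The Sample size section ({14}) of the protocol article makes three linked statements.

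- The power calculation (80% power, 5% alpha) ends with "resulting in a required sample size of 42 participants in total".
- To allow for dropout, "the number of participants was increased by 25%, resulting in approximately 18 participants per study arm".
- The next sentence justifies the allowance: "This dropout rate is common for therapist-guided internet-based interventions".

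The only rate that the third statement can refer to is the 25% in the second. The Trial design section ({8}) adds that "Participants will be randomized to all groups equally", so 42 in total means 14 per arm and 18 per arm means 54 in total. The protocol gives no other dropout rate and no other recruitment target.

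**The concern.** The plan uses one figure, 25%, in two roles: as the proportion added to the required number, and as the proportion of participants expected to be lost. These are different quantities. Adding a fraction d to a required number n and then losing the same fraction d leaves n(1 + d)(1 − d) = n(1 − d²), which is always below n. To keep n completers after losing a fraction d, n must be divided by (1 − d).

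What is at stake is whether the recruitment target delivers the stated 80% power when dropout runs at the rate the protocol itself calls common. If it does not, the justification of the sample size is wrong as written, whatever one thinks of the figure of 42.

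**Working it through.** **Inputs, all from Sample size {14} except the allocation ratio, which is from Trial design {8}**

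- Required number: 42 in total, 14 per arm
- Dropout allowance: 25%
- Stated target: about 18 per arm
- Allocation: 1:1:1

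**Step 1. Reproduce the plan's figure.** Multiplying: 42 × 1.25 = 52.5; 52.5/3 = 17.5 per arm; rounded up, 18 per arm, or 54. This is the stated target, so the allowance was made by multiplication.

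**Step 2. Apply the stated dropout to the stated target.** 54 × 0.75 = 40.5 in total, or 18 × 0.75 = 13.5 per arm. The requirement is 42, or 14 per arm. The shortfall is 42 − 40.5 = 1.5 completers.

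**Step 3. Find the dropout that the target does cover.**

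- For 54 randomised: 1 − 42/54 = 22.2%. Per arm, 18 can lose four and keep 14; a fifth loss leaves 13.
- For the unrounded 52.5: 1 − 42/52.5 = 20.0%. Rounding up to whole arms therefore already supplies the difference between 20% and 22.2%.

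**Step 4. Inflate by division.** 42/(1 − 0.25) = 56; 56/3 = 18.67 per arm; rounded up, 19 per arm, or 57. Check: 57 × 0.75 = 42.75, which is at least 42.

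| Randomised | Per arm | Left after 25% loss | Dropout covered for 42 completers |
|---|---|---|---|
| 54 (plan) | 18 | 40.5 | 22.2% |
| 57 | 19 | 42.75 | 26.3% (1 − 42/57) |

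**Step 5. Cost in power.** The protocol states no standard deviation, so the 42 cannot be reproduced. The effect of the shortfall can still be found by assuming that 14 per arm gives exactly 80% power.

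For a pairwise non-inferiority comparison with a normal approximation and no true difference, power = Φ(Δ/(σ√(2/n)) − z₁₋α), where Δ is the margin. Moving from 14 to 13.5 per arm multiplies the first term by √(13.5/14) = 0.982, so σ and Δ cancel. The protocol does not say whether the 5% alpha is one-sided, so both cases are shown.

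- One-sided 5%: first term at n = 14 is 1.645 + 0.842 = 2.486; at 13.5 it is 2.441; power = Φ(2.441 − 1.645) = 78.7%.
- One-sided 2.5%: 1.960 + 0.842 = 2.802 becomes 2.751; power = Φ(2.751 − 1.960) = 78.6%.
- Three-group ANOVA F test at 5%, with the effect size set to give 80% at 14 per arm (Cohen's f = 0.498): power at 13.5 per arm = 78.3%.

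The loss is thus 1.3 to 1.7 percentage points.

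**The case against.** The strongest reply is that the operation described was carried out correctly: the number was to be raised by 25%, and it was. On this view only the label is loose, since a 25% increase corresponds to a 20% loss among those randomised. The authors may have had such a rate in mind, and then the target is sound and one sentence is badly worded. This cannot be ruled out. But neither 20% nor 22% appears anywhere in the protocol, and the sentence that follows calls the figure a dropout rate. The text needs correcting on either reading.

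Four further points can be made.

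- **The target is given only as approximate.** This does not help: 17.5 rounds to 18, but 18.67 rounds to 19.
- **The Implementation section ({16c}) speaks of 60 participants.** That is an example of how the allocation list is built, not a target. It does show that allocation is not capped at 54.
- **Dropouts need not be lost to analysis.** Under {18b}, participants who discontinue are still asked for follow-up questionnaires, and {20c} allows multiple imputation for the intention-to-treat analysis. This stands in part: stopping treatment is not the same as a missing outcome. But {20c} also bases results on the per-protocol approach, which these measures do not protect, and imputation does not replace the information that was lost.
- **The effect is very small.** This stands in full. A loss of 1.3 to 1.7 points of power is slight beside the uncertainty of a required number for which no standard deviation is given. That basis is a separate question, and this point gains no weight from it.

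**Conclusion.** The sample-size statement is wrong as written. Under the protocol's own 25% dropout, 54 randomised leaves 40.5 completers, not 42; the target that meets the stated aim is 57. The conclusion takes the 42 as given, reads the 25% as the expected loss among those randomised, and assumes equal loss across arms.

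In size this is a minor error. Power would be about 78.3% to 78.7% instead of 80% if the full 25% are lost, and the requirement is met in full for losses up to 22.2%. It is worth correcting because the recruitment target rests on it and the correction costs almost nothing. It is not a serious loss of power.

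**What to change.** Choose one of two corrections in Sample size {14}.

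1. **Keep 18 per arm.** State that 54 randomised leaves 42 completers if dropout is no more than about 22%, and remove the description of 25% as the dropout rate. This costs one sentence.
2. **Keep the 25% dropout rate.** State the calculation as 42/(1 − 0.25) = 56, rounded up to 19 per arm (57). This costs three more participants than planned.

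According to Trial status, recruitment had not begun, and {16b} and {16c} have the allocation list generated only once recruitment is complete, so on the document's own timeline the second option needs no change to the randomisation procedure. If recruitment has since closed, the first option still applies, with the number actually randomised in place of 54.

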### Objectives {7}

The purpose of this study is to assess the efficacy of Internet-delivered cognitive behavioral therapy (CBT) and Internet-delivered mindfulness-based tinnitus stress reduction intervention for adults with tinnitus, by comparing their efficacy against each other and against a waiting list control group.

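### The non-inferiority claim has no test that can decide it: the article names only ANOVA, and its unsided 5% alpha leaves the confidence level for the 7-point margin open

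*Protocol article*

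**What the plan says.** Trial design {8} states: "This study is three-armed parallel-group randomized controlled non-inferiority trial". The abstract's discussion says the same of the comparison between ICBT and iMBTSR. Objectives {7} puts the aim symmetrically, "by comparing their efficacy against each other and against a waiting list control group".

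Sample size {14} gives the only error rate for the primary comparison: "In order to attain 80% power with a 5% alpha level, a three-means non-inferiority test (ANOVA) was performed". It then names the endpoint and the margin: "The primary end point used for the non-inferiority test was the THI score at 8 weeks, and the equivalence margin was determined to be 7" (in THI units), taken from a minimal clinically important difference in an earlier study. No SD or effect size is given. The result is 42 participants, raised by 25% to about 18 per arm.

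Statistical methods for primary and secondary outcomes {20a} plans repeated-measures ANOVAs to assess change and to compare the intervention groups and the control group, together with effect sizes and a regression for predictors. It mentions neither the margin nor a confidence interval.

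**The concern.** A non-inferiority claim rests on one directional comparison of two arms: is the new programme worse than the reference by less than the margin? An ANOVA F test asks whether a set of means, or their changes over time, differ at all. A significant F does not refute non-inferiority. A non-significant F does not establish it. Both places in the article that name a method for the primary outcome name ANOVA.

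A reader who sets the ANOVA label aside and applies the 7-point margin still needs a confidence level. A 5% alpha can mean a one-sided 5% test, which matches a two-sided 90% interval. It can also mean a two-sided 5% level, of which only one 2.5% tail bears on non-inferiority, and that matches a 95% interval. The same week-8 THI result can pass one and fail the other. The trial is open label and its analysts will not be blinded (Who will be blinded {17a}), so the rule should be on record before data are seen.

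**Working it through.** **Inputs from the article.** Alpha 5%, power 80%, margin 7 THI points, total 42, equal allocation (so 42/3 = 14 per arm), and 25% added for dropout (42 × 1.25 / 3 = 17.5, about 18 per arm, as stated).

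**Inputs assumed.** SD of week-8 THI: 10, 15 or 20. Difference d = iMBTSR minus ICBT; a higher THI is worse, so positive d means iMBTSR is worse. True difference 0.

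**The stated 42.** It cannot be reproduced, because the article gives no SD. It also does not reveal the sidedness. By the normal approximation at 14 per arm, SD = 7 / [(z for alpha + 0.842) × √(2/14)]. That gives SD 7.45 for one-sided 5% and 6.61 for one-sided 2.5%. Either value would yield 42, so nothing further is inferred from it.

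**Step 1: the F test ignores the margin.** Take ICBT at 0, the waiting list 15 points worse (assumed), SD 10 and 14 per arm. F = 14 × (sum of squared deviations of the three means) / 2 / 100, on 2 and 39 df.

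- d = −3: sum of squares 186.0, F = 13.0
- d = +1.7: sum of squares 134.9, F = 9.4
- d = +8: sum of squares 112.7, F = 7.9

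All three have p < 0.01. The last lies beyond the 7-point margin, yet the F test gives the same answer as for the first two. This is the simple three-mean version. A group-by-time F test on the same arms likewise has no direction and no margin.

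**Step 2: the level changes the cut-off.** Non-inferiority passes if d + t × SD × √(2/14) < 7. With 26 df, t = 1.706 (one-sided 5%) or 2.056 (one-sided 2.5%). At SD 10 the standard error is 10 × 0.378 = 3.78. The cut-offs are 7 − 1.706 × 3.78 = 0.55 and 7 − 2.056 × 3.78 = −0.77. So an observed difference of exactly 0 passes with the 90% interval (−6.45 to 6.45) and fails with the 95% interval (−7.77 to 7.77).

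**Step 3: how often the verdict differs.** The chance of passing is the noncentral t probability with noncentrality 7 / standard error.

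| Assumed SD | Passes at one-sided 5% if d below | Passes at one-sided 2.5% if d below | Chance of passing, 5% | Chance of passing, 2.5% | Passes first, fails second |
|---|---|---|---|---|---|
| 10 | 0.55 | −0.77 | 56.3% | 43.0% | 13.3% |
| 15 | −2.67 | −4.65 | 32.9% | 22.0% | 10.9% |
| 20 | −5.89 | −8.54 | 22.9% | 14.3% | 8.6% |

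With all 18 per arm retained, the last column becomes 12.8%, 11.8% and 9.5%.

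**The case against.** **Sidedness is a detail for the analysis plan.** A condensed article commonly leaves the side of the alpha and the interval level to a full protocol or analysis plan, and neither is shown here. This stands for the missing side taken alone. It also means a reader cannot infer that the level will be picked after the data are seen. It does not dispose of the point, because the article does name a test for the primary comparison, and the test it names cannot decide the claim.

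**An ANOVA model could supply the interval.** True: a contrast between two arms with its interval can be taken from such a model. But neither section that names the ANOVA mentions a contrast, an interval or the margin in the analysis.

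**The word equivalence.** A reader might infer that the trial also tests equivalence, so that a clear advantage for iMBTSR would count as failure. The documents do not support this. The word occurs once, in the sentence that names the non-inferiority test, and no lower bound or equivalence hypothesis appears anywhere.

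**The origin of 42.** A reader might infer that 42 came from a plain three-group F test, since an assumed f = 0.5 gives 80.3% power at 42. That effect size is not a standard benchmark. A group-by-time interaction with three groups, two time points, f = 0.25 and correlation 0.5 (also assumed) gives the same power at 42. The article does not say which calculation was run.

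**The reference arm.** It is not named in a decision rule, but the background treats CBT as established and mindfulness as emerging, so ICBT as reference is fairly implied.

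**The low pass rates.** At SDs of 10 to 20 these mostly reflect a small trial. Only the last column of the table belongs to this point.

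**Conclusion.** The point holds in limited form. The plan as written ties the non-inferiority claim to an ANOVA, which has neither a direction nor a 7-point margin. The unsided 5% then leaves two defensible confidence levels. That second ambiguity changes the conclusion in about 9 to 13% of trials at 14 per arm with no true difference. The figure rests on assumed SDs of 10 to 20 and a two-arm t comparison. Equivalence margin is a wording error and not a second hypothesis, and no conclusion is drawn about how 42 was obtained. The matter is worth correcting because the headline claim depends on it and the correction is nearly free.

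**What to change.** In Sample size {14}, write non-inferiority margin and drop the three-means ANOVA label for this test. State one rule there, and repeat it in section {20a}: iMBTSR is non-inferior to ICBT (reference) if the upper limit of the two-sided 95% confidence interval for the iMBTSR minus ICBT difference in week-8 THI is below 7 points (one-sided 2.5%). If one-sided 5% was intended, say so and use the 90% interval throughout. Keep the repeated-measures ANOVAs for the comparisons with the waiting list.

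The cost is a few sentences in the protocol and the register before data are seen. The 95% rule is somewhat stricter. If the SD were 7.45 (assumed; the value at which 14 per arm gives 80% at one-sided 5% by the normal approximation), the standard error is 7.45 × 0.378 = 2.82 and 7/2.82 = 2.49. Power at one-sided 2.5% is then the normal probability below 2.49 − 1.96 = 0.53, about 70%. Restoring 80% would take 14 × (1.960 + 0.842)² / (1.645 + 0.842)² = 17.8, so 18 evaluable per arm. Whichever level is chosen, the SD should be stated and the sample size recomputed to match.
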